#### ARM

This is a well-established methodology that provides a direct assessment of anal sphincter pressure and anorectal coordination during simulated defaecation. ARM is widely available, easy to perform and well accepted by participants. ARM will be repeated with TCSCS according to the protocol for TCSCS application as described above. Stimulation frequency, location and intensity during ARM will be guided by the results of the Baseline EMG Mapping of Spinal Cord Segments performed during visit 3 and by our ability to activate S2-S4 innervated muscles (spinal cord segments crucial for anorectal sphincter control).

#### 24 hrs BP monitoring (on day of bowel routine):

A 24-hour ABPM will be performed using the Meditech Card(X)plore (Meditech Ltd., Budapest, Hungary), a well-established clinical protocol on a day the participant completes a bowel routine.. Compared to a single one-time clinic visit, 24-hour ABPM has been found to provide a highly effective and comprehensive assessment of true blood pressure and heart rate. Briefly, a standard adult-sized cuff for an arm circumference of 24-32 cm will be fixed on the non-dominant arm. A mercury sphygmomanometer comes attached to the monitor and recordings will be taken every 15 minutes between 0700-2300, which represents the daytime period, and then every hour from 2300-0700, which represents the night-time period. Daytime and night-time values will be determined from the average of all measurements during each time period. All participants will be asked to complete an activity log to

indicate the time before and after each CIC, transfers, time they transferred into supine position to sleep then seated when they woke-up, or any other times they felt AD occurring. Additionally, all participants will be instructed to manually record a BP measurement during each event by pressing the button '1' followed by the button '2' located on the front of the ABPM device. Participants will be instructed to maintain their routine activities while avoiding exercise and excessive physical exertion. Participants will be also requested to avoid scheduling their regimented bowel routine (as a common AD trigger) on the same day of wearing the ABPM. Prior to starting 24-hour ABPM, three consecutive baseline measurements (separated by one minute) will be recorded with the participant seated in their own wheelchair, following five minutes of rest. The average of three measurements blood pressure and heart rate) in the seated position will be used as the baseline from which the presence or absence of AD bouts during the daytime 24-hour ABPM period will be determined. Any measurement that had a systolic blood pressure  $\geq 20$  mm Hg above the average seated baseline value will be documented as a bout of AD, and the corresponding cause was obtained from the activity log. AD severity will be calculated by subtracting the highest recorded systolic blood pressure from the respective baseline. Calculation of AD during the night required another baseline BP due to change in position from seated to supine and due to a physiological nocturnal dip that is found absent in those with motor-complete tetraplegia. A nocturnal dip is described as a physiological circadian blood pressure pattern where blood pressure is reduced by 10% during sleep. Participants will be given a diary to log their activities while wearing the 24 hour blood pressure monitor.

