#### Visit 2: Baseline Assessments – Weeks 3-4:

Approximately 1 hour.

All eligible participants will undergo baseline evaluation for severity of bladder, bowel, sexual and cardiovascular dysfunctions using the validated questionnaires listed below. Participants will also undergo baseline 24 hours ambulatory evaluation of cardiovascular functions. This test will be specifically scheduled on the day of bowel routine with detailed documentation of time of bowel routine and each of the bladder catheterisations.

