### *Cardiovascular assessments*

- 24 hrs BP monitoring (on day of bowel routine):
- 24 hrs diary of activities

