### *Visits 7 – 18 or 36: Long Term TCSCS – Weeks 7-12:*

Approximately 90 minutes per visit.

Participants will come to ICORD for long term TCSCS, either 2 days/week (moderate) or 5 days/week (intense) for 6 weeks for a total of either 12 sessions or 30 sessions. Please see Description of Assessments for the details of an individual session.

During the 6 weeks of long term TCSCS, TNFBM will be measured during participants' conventional bowel routines at home. Participants will be asked to record the time from 'suppository insertion' to 'when bowel evacuation is completed' once per week for the bowel movement completed mid-week during each week of the 6 week TCSCS pathway.

24 ABPM will be performed mid-way through the 6 weeks and during the final week of the 6 weeks of treatment in combination with the participants' bowel routine.

## Visit 19-20 OR 37 – 38: Immediate Post-TCSCS Assessments – Week : 13

Visit 19 or 37 (approximately 3 hours):

After the 6 weeks of TCSCS, all participants will complete 1 visit at ICORD including UDS assessments and a SCI severity assessment (ISNCSCI). Please see description of Assessments for details.

Visit 20 or 38 (approximately 1 hour):

A series of questionnaires on low urinary tract function, bowel function, cardiovascular function and sexual health will be conducted by telephone or video conference call (considering the present COVID-19 pandemic environment). The questionnaires are listed below and details can be found in the Description of Assessments Section.

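### The protocol puts 24-hour blood pressure monitoring on a bowel-routine day, then asks participants in the same procedure section to keep the bowel routine off that day

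*Protocol*

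**What the plan says.** The Protocol ties the ABPM to a bowel-routine day in four places:

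- Visit 2, Baseline Assessments: the test is to be "specifically scheduled on the day of bowel routine with detailed documentation of time of bowel routine and each of the bladder catheterisations".
- The Cardiovascular assessments list for Visit 2: "24 hrs BP monitoring (on day of bowel routine").
- Visits 7 – 18 or 36, Long Term TCSCS: the ABPM is done mid-way through the six weeks and "during the final week of the 6 weeks of treatment in combination with the participants' bowel routine".
- The ABPM procedure section under Descriptions of Assessments carries the bowel-routine day in its heading, and its first sentence puts the recording "on a day the participant completes a bowel routine".

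Further down that procedure section, participants are asked to "avoid scheduling their regimented bowel routine (as a common AD trigger) on the same day of wearing the ABPM".

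The section also defines what is read from the recording. Any systolic value at least 20 mmHg "above the average seated baseline value will be documented as a bout of AD", its cause is taken from the activity log, and severity is the difference between the highest systolic reading and baseline.

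**The concern.** The two instructions are opposites, and they concern the exposure that the recording is meant to observe. The avoidance sentence itself calls the bowel routine a common AD trigger, and the Background names bowel stimuli among the frequent triggers of severe hypertensive episodes. Whether the routine falls inside the 24 hours can therefore affect both the number of bouts and the peak reading.

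Objective 3 asks whether six weeks of stimulation is safe as well as effective. The protocol has other cardiovascular safety data: beat-by-beat pressure during urodynamics and anorectal manometry, pressure every minute during stimulation sessions, the ADFSCI questionnaire and adverse events. These are clinic-based or self-reported. The ABPM is the only objective measure of blood pressure on an ordinary day, so a fault in how its day is chosen is not made good elsewhere.

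**Working it through.** The protocol gives no figure on this point to reproduce. The check is a comparison of the text.

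**1. Side by side.**

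| Place in the Protocol | Recording | Bowel routine on the ABPM day? |
|---|---|---|
| Visit 2, Baseline Assessments | Baseline | Required |
| Cardiovascular assessments list, Visit 2 | Baseline | Required |
| Visits 7 – 18 or 36, Long Term TCSCS | Mid-course and final week | Required |
| ABPM procedure section, heading and first sentence | All | Required |
| ABPM procedure section, later sentence | All (no visit named) | To be avoided |

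In the Long Term TCSCS row, the bowel-routine phrase could be read as attaching to the final week only. The heading and first sentence of the procedure section cover the mid-course recording in either case. The avoidance sentence is not limited to a visit, so it meets the opposite rule at all three recordings.

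**2. What follows from each way of applying the text.**

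- Routine day every time: the recordings are comparable and include the trigger, as the visit schedule intends.
- Avoidance every time: the recordings are comparable with each other, but bowel-triggered AD is absent from all of them. A safety reading from them would not speak to the situation that the schedule was built to observe.
- A mixture across recordings or participants: a difference in bouts or severity may reflect the type of day and not the stimulation. One qualifying reading makes a bout, and one reading can set severity.

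**3. Can the type of day be recovered afterwards?** Only in part.

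- At baseline, Visit 2 asks for the time of the bowel routine.
- The activity-log events listed in the ABPM section are catheterisations, transfers, going to bed and getting up, and any time AD is felt. The bowel routine is not among them.
- The weekly timing of bowel movements during treatment is done "once per week for the bowel movement completed mid-week during each week". That movement need not fall on the ABPM day.
- A general activity diary is kept and the cause of each bout is read from the log, so many routines would probably be noted. Nothing requires it on treatment.

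**4. Can the effect be sized?** In the daytime, "recordings will be taken every 15 minutes between 0700-2300", so a recording has 16 h × 4 per hour = 64 scheduled daytime readings. Going further needs three quantities: the share of readings during a routine that reach the threshold, the share of recordings made off-routine, and whether that share differs between baseline and treatment. The document gives none of them.

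**The case against.** The strongest reply is that the intent is plain. Four places agree, the baseline text is emphatic, and the avoidance sentence is alone. Parts of that section slip into the past tense, which suggests text carried over from an earlier study, though that is an inference. The instructions that participants actually receive are not in the documents, so which rule reaches them is unknown. This all stands. It makes the sentence easy to correct, but it does not make it harmless, because the sentence describes what participants will be asked to do.

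A reader might go further and infer that the change in AD from baseline to treatment is biased. The document does not support this. Baseline and treatment carry the same pair of rules, and the text offers no mechanism for systematic switching between them. Following either rule throughout leaves the change unaffected by day type. Both dose groups have the same instructions, so the conflict gives no reason for bias between moderate and intensive stimulation. The Objectives, Hypotheses and Outcomes section names no ABPM outcome, and the Statistical Plan lists no ABPM analysis.

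A reader might also try to count affected readings. The Background mentions bowel movements lasting up to two hours, which would span 2 h × 4 = 8 of the 64 daytime readings (8/64 = 12.5%). That duration is a background figure and not a limit for this cohort. A routine at night would meet hourly readings, and the manual readings requested at each logged event come on top. The share that would qualify as bouts is unknown, so the 8 does not convert into a number of bouts.

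Finally, the diary may identify many routine days. That too stands in part: the gap is that the bowel routine is not a required log entry on treatment.

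**Conclusion.** The contradiction is certain and lies in the current text. Its consequence is conditional. If the avoidance sentence is followed, bowel-triggered AD goes unobserved. If the rules are mixed, bouts and peak-based severity are not comparable between recordings or participants. If the visit schedule is followed throughout, neither problem arises.

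The reach is limited to the interpretation of daily-life cardiovascular safety under Objective 3. No named outcome or planned test is affected, and no numerical size can be given from the document. The conclusion assumes only that the bowel routine is a common AD trigger, as the protocol itself says. The sponsor should correct it because it concerns a safety measurement and the remedy is nearly free.

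**What to change.** 1. Delete the sentence asking participants to avoid the bowel routine on the ABPM day, and check that the participant instructions match.
2. State once, in the ABPM procedure section, that the baseline, mid-course and final-week recordings are all worn on a bowel-routine day.
3. Add the start and end times of the bowel routine to the activity-log events at every recording, extending what Visit 2 already asks at baseline.
4. Classify any recordings already made as routine or non-routine day from the diary, and report separately those that cannot be classified.

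The cost is one deleted sentence, one clarified rule and one log entry, with no new visit or procedure. Sorting past recordings concerns at most 40 participants × 3 recordings = 120, and fewer if the trial is still early or participants have dropped out.

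### ABPM rules average event-triggered readings into the day and night means, score readings taken in bed against a seated baseline, and leave the night-time dysreflexia reference undefined

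*Protocol*

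**What the plan says.** All of this is in the protocol section on 24-hour BP monitoring.

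- **Schedule.** Day and night are set by the clock: "recordings will be taken every 15 minutes between 0700-2300, which represents the daytime period, and then every hour from 2300-0700".
- **Period means.** "Daytime and night-time values will be determined from the average of all measurements during each time period". Participants also trigger a manual reading at each logged event (catheterisation, transfers, felt AD). Nothing separates these from the scheduled readings.
- **Baseline.** The only baseline whose collection is described is seated: "three consecutive baseline measurements (separated by one minute) will be recorded with the participant seated in their own wheelchair, following five minutes of rest". Its average "will be used as the baseline from which the presence or absence of AD bouts during the daytime 24-hour ABPM period will be determined".
- **AD rule.** A systolic value at least 20 mmHg "above the average seated baseline value will be documented as a bout of AD, and the corresponding cause was obtained from the activity log". That sentence has no exception for posture or time of day.
- **Night.** "Calculation of AD during the night required another baseline BP due to change in position from seated to supine". The same sentence adds the nocturnal dip as a second reason and says the dip is absent in motor-complete tetraplegia. No source, timing, posture or number of readings is given for this other baseline.
- **Posture log.** Participants record when they lie down to sleep and when they sit up again. No rule uses those times.
- **Severity.** "AD severity will be calculated by subtracting the highest recorded systolic blood pressure from the respective baseline".

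Recordings are planned at baseline (Visit 2), mid-way through the six weeks of stimulation, and in its final week.

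**The concern.** The three recordings are the only objective 24-hour blood pressure record in a study whose Objective 3 asks whether long-term stimulation is safe. Their use lies in comparing one recording with the next, so the derived quantities should change only when blood pressure changes.

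As written, they can change for other reasons. A period mean moves with the number of button presses, because presses cluster at moments of high pressure. The daytime AD count moves with bedtime and rising time, because readings in bed are held against a seated value; the section itself gives this change of posture as a reason for a different baseline. The night-time AD count has no stated reference, and the sentence that applies the seated threshold without restriction conflicts with the statement that night needs another one.

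**Working it through.** The protocol gives no figure to reproduce here. The inputs are its recording schedule, its 20 mmHg rule and its 10% dip. The number and size of event readings, the hours in bed and the posture differences are assumptions, shown as ranges.

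**Scheduled readings.** Day: 16 h × 4 = 64. Night: 8 h × 1 = 8.

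**(a) Pooling of event readings.** If m event readings run r mmHg above the n scheduled ones, the period mean shifts by r × m / (n + m).

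- Day, m = 1, r = 20: 20 / 65 = 0.3 mmHg. Day, m = 4, r = 40: 160 / 68 = 2.4 mmHg.
- Night, m = 1, r = 20: 20 / 9 = 2.2 mmHg. Night, m = 4, r = 40: 160 / 12 = 13.3 mmHg.

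The effect is mainly at night, where there are few scheduled readings. As an example across recordings: at r = 20, going from one night press to four moves the night mean by 80 / 12 − 20 / 9 = 6.7 − 2.2 = 4.4 mmHg (before rounding) with no change in the scheduled readings.

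**(b) Posture within the clock-defined day.** Lying down h hours before 2300 puts 4h scheduled day readings in bed.

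- h = 1: 4 of 64 (6%). h = 2: 8 of 64 (12.5%). h = 3: 12 of 64 (19%).
- Each hour in bed after 0700 adds 4 more.

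Against the seated threshold, the true rise needed to be scored as AD is 20 − (supine − seated). For a supine minus seated difference of −10, 0, +10 or +20 mmHg (assumed), it is 30, 20, 10 or 0 mmHg. The error can therefore hide episodes or create them.

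**(c) Night reference.** If the seated threshold were carried into the night, the rise needed would be (seated + 20) − night level. With the protocol's 10% dip and an assumed seated systolic of 100, 110 or 120 mmHg, the night level is 90, 99 or 108, so the rise needed is 30, 31 or 32 mmHg. With no dip and no posture effect it stays at 20. Eligibility covers injuries at or above T6, so it is not confined to the tetraplegia in which the protocol says the dip is absent. No single offset from the seated value would suit everyone.

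**Severity.** Subtracting the peak from the baseline gives a negative number that becomes more negative as the episode worsens.

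**The case against.** The strongest reply is that most of this is derivation detail of the kind a statistical analysis plan settles, and that such a plan may exist. Hourly night readings and posture times are collected, manual readings could be left out at analysis, and the section cites a published ABPM method that may supply the night rule, although that cannot be checked here.

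For the night reference taken alone, much of this stands. A reader might infer that night-time AD cannot be derived at all. The protocol does not support that: the reference is undefined, not unobtainable. Only if a resting supine reading is intended must the protocol schedule it, since it cannot be recovered afterwards.

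The reply is weaker for the other two items, because there the protocol does state a rule, and following it gives a worse answer. It can fairly be said that the text never states outright that supine daytime readings use the seated baseline, and that severity refers to a respective baseline. Even so, the literal rule has no posture exception.

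A reader might also take all three items as causes of one night-time problem. They are separate: daytime posture affects daytime AD, and pooling affects the period means, which the AD rule does not use. Pooling would reach night AD only if the night mean were adopted as the night reference.

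Larger shifts can be produced, for example 20 × 40 / 84 = 9.5 mmHg by day, but that needs 20 presses each 40 mmHg high, and nothing in the protocol suggests that number.

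**Conclusion.** The point holds as two rules that bias results as written and one reference that is required but undefined. With 1 to 4 event readings 20 to 40 mmHg high, pooling adds 0.3 to 2.4 mmHg to the day mean and 2.2 to 13.3 mmHg to the night mean. With 1 to 3 hours in bed before 2300, 6% to 19% of scheduled day readings are judged against the wrong posture. The reading counts follow from the protocol; the press counts, rises, bedtimes and posture differences are assumptions.

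The importance is modest. ABPM is supporting cardiovascular safety evidence. It is not among the outcomes listed under the objectives, and the Statistical Plan names no ABPM analysis. The severity wording is a reversed sign; a reader might infer that episodes would be misranked, but the magnitude is unaffected and the intent is clear.

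**What to change.** 1. Compute day and night means from scheduled readings only. Keep button-triggered readings for detecting AD and attributing its cause.
2. Assign each reading to a seated or a supine/night reference by the logged lying-down and sitting-up times, and limit the seated threshold to seated readings.
3. Prespecify one night reference that reflects both posture and sleep, for example from scheduled readings in the logged supine period with no logged event. A median would be less affected by an unlogged episode among so few readings. An awake supine reading at fitting would deal with posture only: where the 10% dip occurs, an awake supine value of 110 mmHg (assumed) lies 11 mmHg above the sleeping level, so a rise of 31 mmHg would be needed to flag AD.
4. Define severity as highest systolic minus the matched baseline.
5. Apply the same rules to all three recordings, and fix them before the data are examined.

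The cost is a few sentences of protocol text. The log, the schedule and the manual readings are already planned, so no new measurement is needed. The log does have to be complete enough to give the posture times, and the analysis has to be able to tell manual from scheduled readings.

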### Long Term TCSCS Visits

Each session will last approximately 90 minutes. TCSCS will be delivered using a non-invasive central nervous system stimulator (TESCoN, SpineX Inc., CA, USA). A self adhesive round electrode placed on the skin between spinous processes at the midline over the vertebral column will function as a cathode, and two rectangular self-adhesive electrodes located symmetrically on the skin over the iliac crests as anodes. Specific areas for electrode placement will be examined and prepared to reduce skin impedance. A temperature probe will be positioned adjacent to the cathode in order to monitor changes in skin temperature to prevent potential skin damage. Blood pressure and heart rate will be measured once every minute throughout the. TCSCS will be delivered under the supervision of either [name] or [name], who are both Physical Medicine and Rehabilitation physicians.

### Validated questionnaires

#### Depression screening - Patient Health Questionnaire-9 (PHQ-9)

This scale is a brief, 9-item self-report screening tool that meets the criteria for good diagnostic accuracy for assessing depressive disorders during inpatient SCI rehabilitation. A comprehensive systematic review performed by the Spinal Cord Injury Research Evidence (SCIRE) Team concluded that given the adequate to excellent reliability and validity of this measure there is no requirement to develop an SCI-specific instrument.

Autonomic dysfunction in Spinal Cord Injury (ADFSCI) questionnaire assesses self-reported frequency and severity of autonomic related symptoms. The AD part of the questionnaire includes 10 items, each using a 5-point scale to score the frequency and severity of hypertensive symptoms, such as headache, goose bumps, confusion, etc., under different circumstances.

